## Methods

### Objectives of the study

The primary objectives of the study are to assess whether the HERrespect intervention reduces female garment workers’ experiences of: (i) physical, sexual, and physical and/or sexual intimate partner violence and (ii) workplace violence in Bangladesh.

Additionally, the study will assess whether HERrespect is effective in: (1) increasing gender equitable attitudes, self-esteem, and knowledge and uptake of services for addressing IPV among female garment workers; (2) reducing acceptance of VAWG and the rate of depression among female garment workers; (3) increasing gender equitable attitudes and knowledge regarding laws and policies addressing gender discrimination and workplace violence against women among management; and (4) improving management styles and attitudes towards workers among management.

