Outcomes	Workers become more willing and equipped to engage in respectful dialogue with managers/colleagues at work and intimate partners	Greater gender awareness and sense of empowerment		Less acceptance and normalization of the use of violence	Workers have better coping mechanisms to work stress	Greater awareness on protection mechanism and support for abused women inside and outside the workplace	
Outputs	Workers are better able to communicate their needs at home and at work (i.e. asking for leave, explaining their needs, saying no in respectful ways)	Workers are more aware of how gender shapes their roles and responsibilities, and also how men can become more involved in care responsibilities.	Workers are more aware of how power affects their relationships and interactions with managers and their husbands	Workers can identify both joyful and harmful relationships, as well as ways to ameliorate them	Workers understand the sources of stress at work (collectively) and develop ways to deal with stress	Workers are aware of where to seek help inside and outside the factory	Workers aware of their rights and the responsibilities of the factory and the government
Exercises needed	Active listening; body language; attack, avoid, manipulate; I statements; saying no in respectful ways; assertive responses	Men and women: ideal and reality	Power over; statues of power	Joys and challenges; ways to get hurt; consequences of violence	Managing stress at work	Support systems for abused women; providing support as Change Makers	Factory policies and local laws
Inputs	Critical reflection on different ways of communicating (physical and verbal) through interactive activities	Understanding the impact of gender expectations (on both women and men) in their day-to-day lives	Reflecting on how power affects our relationships, how we communicate, how we make decisions	Sharing of experiences of violence at home, at work, in the communities, and its consequences	Sharing and mapping of the different points of stress at work	Explaining to workers the types of services (medical, legal, counseling, shelter) for abused women	Explaining to workers the factory policies and local laws

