The ten secondary outcomes are being assessed, reflecting hypothesised pathways of change leading to the primary outcomes. Four secondary outcomes focus on gender attitudes and responses to violence:Acceptance of VAWG amongst female garment workers: Acceptance of VAWG among female garment workers is being measured using statements adapted from the Gender Equitable Men (GEM) scale [25] and WHO multi-country study on women’s health and domestic violence against women [26].Gender equitable attitudes of management staff: Gender equitable attitude of the management staff is being measured using statements adapted from the GEM scale [25], WHO multi-country study on women’s health and domestic violence against women [26] and the South African study on men, masculinities, violence and HIV [27].Response to IPV amongst female garment workers: A single item explores women’s help seeking in response to IPV. The question heavily drew upon the WHO multi-country study questionnaire [26] and the SAFE questionnaire [28]. This question will only be asked to those who experienced physical and/or sexual violence during last 12 months.Knowledge of services in response to IPV amongst female garment workers: One question assesses the knowledge of the workers about where to seek help after experiencing IPV.

Two secondary measures assess women’s well-being:5.Self-esteem of female garment workers: The Rosenberg Self-Esteem scale is being used to measure self-esteem [29]. It measures global self-worth by measuring both positive and negative feelings about self. The scale is uni-dimensional and has shown strong convergent validity for men and women from different ethnic groups [30].6.Depression among female garment workers: Depression in the past week is being measured using the Center for Epidemiologic Studies Depression (CES-D) scale used widely in different settings (including Bangladesh) and showing high reliability and validity [31]. Each question is a statement and asked the respondent to answer how many days she has had particular feelings or ideas.

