Severe physical and/or sexual IPV during past 12 months	Questions asked for measuring physical and sexual violence during past 12 months	Never, once, few, many	10	–	–	Binary - never compared to once or more	Decrease
Witnessed or experienced workplace violence	In the past four weeks, how often have you experienced or witnessed a manager call a worker names?	Never, once, 2-3 times, many times	8	0.83		Mean	Decrease
Secondary outcomes							
Gender attitudes and responses to violence							
Acceptance of VAWG among female workers	In your opinion, does a man have good reason to hit his wife if she disobeys him?	4-point Likert: Strongly disagree, disagree, agree, strongly agree	6	0.69	–	Mean	Decrease
Positive gender attitudes among management staff	I think that a woman needs her husband’s permission to do paid work.	4-point Likert: Strongly disagree, disagree, agree, strongly agree	13	–	0.68	Mean	Decrease
Response to IPV	Did you go to any person/place for help when you experienced any physical or sexual violence during last 12 months?	Yes, no	1	–	–	Binary – yes compared to no	Increase
Knowledge of services in response to IPV	Do you know from where one can get help for such experience? If yes, where?	Yes, no	1	–	–	Binary – yes compared to no	Increase
Women’s well-being							
Self-esteem of the female garment workers	At times, You think you are no good at all.	4-point Likert: Strongly disagree, disagree, agree, strongly agree	10	0.76	–	Mean	Increase
Depression among female garment workers during past week	During the past week you thought your life had been a failure.	Rarely or none of the time; some or a little of the time; moderate amount of time; most or all of the time	13	0.87	–	Mean	Decrease
Management knowledge, practices and experiences							
Better management style of management staff	If you do not comply with your supervisor, you will not be rewarded	Very unlikely; Somewhat likely; Very likely	14	0.90	–	Mean	Increase
Correct knowledge regarding laws and policies	Are there laws/policies in this country that protect women from spousal violence?	Yes; no; don’t know	5	–	–	% correct compared to % incorrect	Increase
Positive attitudes regarding laws and policies	To your opinion - “Sexual remark and gesture is an act of workplace violence”	Strongly agree; agree; no opinion; disagree; strongly disagree	5	–		Mean	Increase

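### Objective 1 promises knowledge and uptake of IPV services, but the scoring stated in Table 2 measures neither: it states no use of the place named, and it counts help sought from anyone

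*Protocol article*

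**What the plan says.** Under Objectives of the study, the first additional objective includes increasing "knowledge and uptake of services for addressing IPV among female garment workers".

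The inputs row of Table 1 (theory of change) shows what the programme teaches as services: "Explaining to workers the types of services (medical, legal, counseling, shelter) for abused women". Other cells of that table add help inside the factory and support given by trained Change Makers.

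Under Trial outcomes, two secondary outcomes relate to this objective:

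- **Knowledge of services.** The text says "One question assesses the knowledge of the workers about where to seek help after experiencing IPV". The Table 2 item is "Do you know from where one can get help for such experience? If yes, where".
- **Response to IPV.** The text describes a single item on "help seeking in response to IPV" and restricts who answers it: "This question will only be asked to those who experienced physical and/or sexual violence during last 12 months". The Table 2 item is "Did you go to any person/place for help when you experienced any physical or sexual violence during last 12 months".

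For both rows Table 2 gives yes/no response categories, one item, the scaling "Binary – yes compared to no" and an expected increase.

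**The concern.** The objective is about services; the two scores are about something looser. The knowledge score, as stated, rests on the woman's own claim to know. The answer that would test the claim is part of the printed item, but it has no stated role in the score. The response score counts help from anyone, so it cannot separate going to a clinic or legal service from going to a relative.

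The looseness may not be equal between arms. Only intervention workers attend sessions that cover services. The Blinding section says nobody was blinded, and the interviews are face to face. A woman who has sat through such a session may answer yes more readily, whether or not she could name a service. Change Maker training may also raise help-seeking from peers. That could be a worthwhile effect, but it is not service uptake.

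At stake is the interpretation of two secondary outcomes: a rise in either would be reported against a services objective that the score does not capture.

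**Working it through.** The documents give no figure for these two outcomes, so there is nothing to reproduce. The check is a comparison of passages, followed by illustrations on assumed rates.

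**Step 1. Objective against stated scoring**

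| Objective 1 | Outcome that could serve it | What the stated score needs | What the objective would need |
|---|---|---|---|
| Knowledge of services | Knowledge of services in response to IPV | A yes | A yes plus a recognised service or support named |
| Uptake of services | Response to IPV | Went to anyone or anywhere for help | Went to a service |

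No other outcome listed under Trial outcomes bears on uptake. In the same table, management knowledge of laws and policies is scored by the share of correct answers, so a correctness rule was stated there and not here.

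**Step 2. Illustration for knowledge (assumed rates)**

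Assume 30% in each arm can truly name a service, nobody in control over-claims, and an extra 5 or 10 points of intervention women say yes. Take n = 330 per arm, the requirement before loss to follow-up in the Sample size section.

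- Risk ratio: 0.35/0.30 = 1.17; 0.40/0.30 = 1.33. The true ratio is 1.0.
- Chance of two-sided p < 0.05: Φ[(d − 1.96·se0)/se1], where d is the difference in proportions, se0 its pooled standard error and se1 its unpooled one.
- 30% v 35%: se0 = 0.0365, se1 = 0.0364, giving Φ(−0.59) = 0.28.
- 30% v 40%: se0 = 0.0371, se1 = 0.0369, giving Φ(0.74) = 0.77.

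If 20 points of over-claiming also occur in both arms, the comparison is 50% v 55% or 60%. The ratios shrink to 0.55/0.50 = 1.10 and 0.60/0.50 = 1.20; the chances of significance are 0.25 and 0.73.

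**Step 3. Illustration for help-seeking (assumed rates)**

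The 330 per arm does not apply here, because only women reporting past-year IPV are asked. Assumed denominators, from the planning figures for physical IPV alone: control 330 × 0.56 ≈ 185; intervention 330 × 0.56 × 0.8 ≈ 148. Hold true service use q equal in both arms and let informal help among the other women be 20% in control and 35% in intervention. The scored rate is q + (1 − q) × informal rate.

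- q = 2%: control 0.02 + 0.98 × 0.20 = 21.6%; intervention 0.02 + 0.98 × 0.35 = 36.3%; ratio 1.68; chance of significance 0.84.
- q = 10%: control 0.10 + 0.90 × 0.20 = 28.0%; intervention 0.10 + 0.90 × 0.35 = 41.5%; ratio 1.48; chance of significance 0.73.

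Service use is the same in both arms throughout.

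All the probabilities treat women as independent and ignore clustering within the eight factories. They show what the scoring permits; they are not forecasts.

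**The case against.** **A binary score can be built after the open answer is coded.** Table 2 does not say that a blank or invalid place still counts as yes. The text speaks of knowing where to seek help, and the questionnaire is in an additional file that is not shown. This stands as far as it goes. A reader might infer that the place is collected and then discarded, or that any yes is credited; the documents do not establish either. What remains is that the scoring the article does state gives the place no role and sets no standard for a valid answer.

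**Response to IPV never claims to be service uptake.** It is named and described as help-seeking, and it asks whether the woman went for help. A reader might infer that merely telling a mother or neighbour would count; the wording does not support that. In-factory and Change Maker support is also part of the programme, so replacing the outcome with formal-service use could exclude help that the programme promotes. This stands too, and it is why the repair belongs in the objective. It leaves the uptake wording of objective 1 with no outcome behind it.

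**The magnitude is assumed.** The knowledge scenario requires no true gain from sessions that teach about services and, in its main form, no over-claiming in control. This is correct, and over-claiming in both arms reduces the ratios as shown. The mismatch itself does not depend on these rates.

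**The consequence is limited.** These are two of ten secondary outcomes, and neither set the sample size. The Limitations section already notes reliance on self-report, although it discusses only under-reporting.

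**Conclusion.** The concern holds as a mismatch between objective 1 and the scoring stated in Table 2. An increase on either secondary outcome could arise without any change in knowledge or use of services.

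The size is unknown. On the assumed rates, a null effect on knowledge could appear as a risk ratio of 1.10 to 1.33, and a null effect on service use as 1.48 to 1.68. Those ranges rest wholly on assumed over-claiming and informal help-seeking that differ by arm.

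A reader might go further and conclude that these outcomes will be biased, or that the trial's main result is in doubt. The documents support neither: they give no rates for these items, and the primary IPV and workplace violence outcomes do not use them. The change is worth making because it is cheap and, on the article's timeline, could be settled before the endline of September to November 2018.

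**What to change.** 1. **Knowledge of services.** Score yes only when the place named matches at least one entry on a code list. Fix the list before endline and apply it to baseline and endline alike. Include medical, legal, counselling and shelter services, together with the in-factory and NGO supports that the programme teaches. State the rule in Table 2.
2. **Response to IPV.** Keep it as help-seeking from any person or place, and change objective 1 from uptake of services to help-seeking.
3. **Formal-service use.** If the baseline questionnaire recorded where women went, report use of formal services as a separate result. A code added at endline only would have no baseline counterpart, whereas the analysis section adjusts for baseline rates.

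The cost is some recoding of an answer that the printed knowledge item already asks for, plus edits to Table 2 and objective 1. The drawback is lower yes rates on the knowledge outcome.

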### Sample size

For the worker survey, the sample size calculation was based on the primary outcome – physical IPV against female garment workers. Expecting 56% baseline prevalence of past year physical IPV experienced by the female garment workers (icddr,b unpublished data), and anticipating a 20% effect size, 5% level of significance and 80% power, the required sample size was 330 workers for both the intervention and control groups. To account for a 20% lost to follow up the sample size increased to 396 workers for both the groups, which was rounded up to 400. Thus, a sample of 100 workers would be required from each of the intervention and control factories, giving 800 in total.

For the management survey, the sample size calculation was based on gender inequitable attitudes among garment management staff. Anticipating 50% baseline prevalence of high or moderate gender equitable attitudes among the management staff, a 30% effect size, 5% level of significance and 80% power, the required sample size was 183 management staff for both intervention and control groups. Anticipating 10% loss to follow up, the sample size increased to 200 for both the groups. Thus a sample of 50 management staff would be required from each of the intervention and control factories, giving 400 in total.

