### Trial design

The trial employs a quasi-experimental design. It is being conducted in four intervention and four control factories. In the intervention factories a randomly selected cohort of married female line workers, a cohort of male line workers, and all middle management staff received the main intervention. In addition, factory-wide campaigns were carried out, and a community activity in one intervention community. For the evaluation, two cohorts have been established and will be followed up over 24 months in each of the intervention and control factories. One is a cohort of randomly selected female line workers (100 per factory) and the second is a cohort of selected management staff with frequent interaction with workers (50 in each factory). Two different questionnaires are administered for workers and management staff (see Additional files 1 and 2). All the workers and management staff from these cohorts were interviewed at baseline, and will be interviewed in the endline. The baseline was conducted before the intervention started, while the endline will be conducted 24 months post-baseline.

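### The 80% power stated for both surveys makes no allowance for factory clustering or for having only four factories per arm, so it is not supported

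*Protocol article*

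**What the plan says.** Under Sample size, the worker calculation rests on physical IPV: "Expecting 56% baseline prevalence of past year physical IPV experienced by the female garment workers", and "anticipating a 20% effect size". The result is "5% level of significance and 80% power, the required sample size was 330 workers for both the intervention and control groups". Loss to follow-up is then added: "To account for a 20% lost to follow up the sample size increased to 396 workers for both the groups". This is rounded to 400 per arm and divided among the factories: "a sample of 100 workers would be required from each of the intervention and control factories, giving 800 in total".

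The management calculation assumes 50% at baseline and a 30% effect: "5% level of significance and 80% power, the required sample size was 183 management staff" per arm, raised to 200 for 10% loss, or 50 per factory.

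Under Trial design: "It is being conducted in four intervention and four control factories", and "One is a cohort of randomly selected female line workers (100 per factory". Recruitment and allocation explains that each factory joined an arm according to its own preference. The data analysis section makes the primary contrast one between intervention and control factories, using binary regression adjusted for baseline rates.

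Sample size mentions no ICC, no design effect and no allowance for the number of factories. The only threat to power that Limitations names is loss to follow-up.

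**The concern.** Workers or managers in one factory share supervisors, policies, a labour pool and a neighbourhood, and much of the intervention works at factory level (campaigns, policy review, sessions for all middle management). Their outcomes are likely to be correlated to some degree. With arm fixed by factory, that correlation inflates the variance of the arm comparison. With eight factories, the between-factory variance is also estimated on few degrees of freedom. A calculation for independent individuals leaves out both effects.

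At stake is how the endline results are interpreted. A reader who takes 80% at face value may give a non-significant result more weight against a 20% reduction than the design can bear.

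**Working it through.** **1. Reproduce the printed figures.** Inputs from Sample size: two-sided 5% (the article does not state sidedness, but two-sided reproduces the figure), 80% power, and 56% falling by a relative 20% to 44.8% (difference d = 0.112).

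n = [1.96·√(2·p̄·q̄) + 0.8416·√(p₁q₁ + p₂q₂)]² / d², then with continuity correction n′ = (n/4)·[1 + √(1 + 4/(n·d))]².

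- Workers: n = 311.7. 4/(311.7 × 0.112) = 0.1146, so n′ = 329.3, which rounds up to 330, as printed.
- Managers, 50% against 65% (35% gives the same): n = 169.3 and n′ = 182.4, which rounds up to 183, as printed.
- Reading the worker effect as 20 percentage points (56% to 36%) gives only 97 to 107 per arm, so the relative reading was used.

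Both figures match with a design effect of exactly 1. No clustering allowance can be hidden in them.

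**2. Power with four factories per arm.** Assumed: m = 80 workers followed per factory (100 less 20%), m = 45 managers (50 less 10%), and a range of ICCs, because the article gives none.

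DE = 1 + (m − 1)·ICC; SE = √[(p₁q₁ + p₂q₂)·DE/(4m)]; power from the noncentral t with 2 × (4 − 1) = 6 degrees of freedom and noncentrality d/SE.

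Example, workers at ICC 0.01: DE = 1 + 79 × 0.01 = 1.79; effective n = 320/1.79 = 179 per arm; SE = √(0.4937 × 1.79/320) = 0.0526; d/SE = 2.13; power 43%.

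| ICC (assumed) | Workers: DE | Workers: effective n per arm | Workers: power, 6 df | Workers: power, normal reference | Managers: power, 6 df |
|---|---|---|---|---|---|
| 0 | 1.00 | 320 | 66% | 81% | 68% |
| 0.005 | 1.40 | 229 | 53% | 67% | – |
| 0.01 | 1.79 | 179 | 43% | 56% | 53% |
| 0.02 | 2.58 | 124 | 32% | 42% | 43% |
| 0.05 | 4.95 | 65 | 19% | 25% | 28% |

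At ICC 0.001, workers have 63% on 6 df and 78% with a normal reference.

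**3. Minimum detectable effect, workers.** The relative reduction detectable with 80% power on 6 df is about 24% at ICC 0, and 31%, 37% and 50% at ICC 0.01, 0.02 and 0.05, against the planned 20%.

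**4. Sensitivity.**
- No loss at all (100 workers per factory): 48% at ICC 0.01 and 20% at ICC 0.05 on 6 df.
- Baseline adjustment, taking an assumed factory-level correlation r of 0.5 to 0.8 and DE = (1 − ICC) + m·ICC·(1 − r²): for ICC 0.01 to 0.05, about 23% to 56% on 6 df, or 29% to 71% with a normal reference.

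**The case against.** The strongest reply is that the low power figures are conditional. No ICC appears in the article. The outcome behind the worker calculation is violence by a husband, at home, so the factory ICC could lie below 0.01. Part of the shortfall also comes from the choice of test: at ICC 0, moving from a normal reference to 6 df alone takes worker power from 81% to 66%. The plan adjusts for baseline in a cohort measured twice, which an unadjusted factory-level test ignores. All of this stands. A reader might infer that the design delivers some 20% to 45% power. The article does not support that as a fact; it is the worker result under one set of assumptions.

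Two other strong readings also go too far. One is that a null result will be presented as ruling out a 20% reduction. The article says no such thing, and Limitations already warns about dilution and attrition. The other is that the analysis will ignore factories. The article names no factory term, but a fuller analysis plan might. If factories were ignored, the nominal 80% would not be power at the 5% level either: the actual type I error, 2·Φ(−1.96/√DE) with 80 per factory, would be about 14% at ICC 0.01 and 38% at ICC 0.05.

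The reply does not rescue the 80%. Nor can it be said that a condensed article left out a design effect, since the printed sample sizes leave no room for one.

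**Conclusion.** The point holds in this form: 330 and 183 per arm are individual-level sample sizes, and the 80% power attached to them is not supported for a comparison of four factories with four. That part is certain from the article's own figures.

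The size of the shortfall depends on assumptions. With ICC 0.01 to 0.05 and an unadjusted test on 6 df, power is about 43% to 19% for workers and 53% to 28% for managers. On 6 df both surveys fall short of 80% even at ICC 0. For workers, only an ICC of about 0.001 or less combined with a normal-reference test comes close. Baseline adjustment narrows the gap but does not close it in the worker scenarios examined at ICC 0.01 or above.

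**What to change.** Keep the sample. For both surveys, replace the 80% statement with power and minimum detectable effect for four clusters per arm and 6 df, tabulated over a range of ICCs (for example 0 to 0.05), with and without baseline adjustment.

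Report the baseline factory ICC with its confidence interval as a guide, not as a single plug-in value. With eight factories of 100 workers and a true ICC of 0.01, simulated estimates spread over about −0.006 to 0.036 (95% range), and 19% fall at or below zero. One such estimate could appear to restore the 80% figure.

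Add to Limitations that clustering within eight factories lowers power, so a non-significant result does not exclude a 20% reduction.

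The cost is a text change and a small calculation on baseline data already collected. The stated power becomes less favourable.

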## Results

A total of eight factories (four intervention and four control) were recruited for the HERrespect study. A total of 800 female garment workers and 395 management staff were successfully interviewed during the baseline survey.

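### The worker sample was inflated for 20% loss by multiplying by 1.2 instead of dividing by 0.8, so 400 per arm leaves 320, short of the required 330; the manager sample also falls short

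*Protocol article*

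**What the plan says.** All the planning figures are in the Sample size section of the protocol article.

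- **Workers.** The inputs are: "Expecting 56% baseline prevalence of past year physical IPV experienced by the female garment workers", and "anticipating a 20% effect size, 5% level of significance and 80% power". From these, "the required sample size was 330 workers for both the intervention and control groups". The attrition step follows: "To account for a 20% lost to follow up the sample size increased to 396 workers for both the groups". This is rounded up to 400, that is 100 in each of four factories per arm and 800 overall, so 330, 396 and 400 are all per-arm figures.
- **Managers.** With 50% baseline prevalence, a 30% effect, 5% significance and 80% power, 183 per arm are required. Then: "Anticipating 10% loss to follow up, the sample size increased to 200 for both the groups". That is 50 per factory and 400 overall.
- **Achieved.** The Results section reports: "A total of 800 female garment workers and 395 management staff were successfully interviewed during the baseline survey". Table 3 splits these as 400 and 400 workers, and 195 (intervention) and 200 (control) managers.

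**The concern.** An allowance for loss is meant to leave the required number at endline. If a fraction d is lost, the number to recruit is n/(1 - d). Multiplying by (1 + d) always gives too few, and the gap widens as d grows. The worker figure of 396 is exactly 330 x 1.2.

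A reader of the Sample size section would conclude that the study can lose 20% of workers and 10% of managers and still meet its own requirement. It cannot. The margin matters here because the Limitations section relies on loss having been allowed for, and also fears that more workers and managers will leave than expected. Under Cohort tracking, workers are contacted every two months, but managers are not tracked by the research team, so their thinner margin has no active follow-up behind it.

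**Working it through.** **Step 1. Reproduce the plan's base sizes.** The section names no formula. The two-sided comparison of two proportions with continuity correction gives both figures. With d = |p1 - p2| and p the mean of p1 and p2:

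- n' = [1.960 x sqrt(2p(1-p)) + 0.842 x sqrt(p1(1-p1) + p2(1-p2))]^2 / d^2
- n = (n'/4) x [1 + sqrt(1 + 4/(n'd))]^2

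| | p1 | p2 (effect read as relative) | n', rounded up | n, rounded up | Plan |
|---|---|---|---|---|---|
| Workers | 0.56 | 0.56 x 0.8 = 0.448 | 312 | 330 | 330 |
| Managers | 0.50 | 0.50 x 1.3 = 0.65 | 170 | 183 | 183 |

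Other readings fail for workers. One-sided gives 246 or 263 (without and with correction), and a two-sided absolute 20-point reduction gives 97 or 107. The base sizes are therefore right for the stated inputs, and the fault lies in the attrition step alone.

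**Step 2. The attrition step.**

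| | Workers | Managers |
|---|---|---|
| Required per arm | 330 | 183 |
| Stated loss | 20% | 10% |
| n x (1 + d) | 330 x 1.2 = 396 | 183 x 1.1 = 201.3 |
| n / (1 - d) | 330/0.8 = 412.5, so 413 | 183/0.9 = 203.3, so 204 |
| Set in the plan | 396, rounded to 400 | 200 |
| Left after the stated loss | 400 x 0.8 = 320 | 200 x 0.9 = 180 |
| Shortfall against required | 10 | 3 |

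The 396 itself would leave 396 x 0.8 = 316.8. For managers the section does not show how 200 was reached; it lies below both 201.3 and 203.3.

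**Step 3. Loss the achieved sample can bear.**

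- Workers: 1 - 330/400 = 17.5%, or 70 per arm.
- Managers, arm of 200: 1 - 183/200 = 8.5%.
- Managers, arm of 195: 1 - 183/195 = 6.2%. At 10% loss this arm keeps 195 x 0.9 = 175.5.

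**Step 4. Power after the stated loss.** The same method turned round, with no clustering:

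power = Phi{ [d - 1/n - 1.960 x sqrt(2p(1-p)/n)] / sqrt([p1(1-p1) + p2(1-p2)]/n) }

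For workers at n = 320: (0.112 - 0.0031 - 0.0775)/0.0393 = 0.80, and Phi(0.80) = 0.788.

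| n per arm | With correction | Without correction |
|---|---|---|
| Workers 330 | 80.1% | 82.2% |
| Workers 320 | 78.8% | 81.0% |
| Managers 183 | 80.1% | 83.0% |
| Managers 180 | 79.4% | 82.4% |
| Managers 175.5 in both arms | 78.3% | 81.4% |

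The manager arms would actually be 175.5 and 180. Their harmonic mean is 2 x 175.5 x 180/355.5 = 177.7, which gives about 78.9% with the correction.

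**The case against.** The strongest reply is that little turns on this. Worker power falls by 1.3 points (80.1% to 78.8%) and planned manager power by 0.7 points (80.1% to 79.4%). Recruitment is over, and no choice of design or analysis depends on it. That is fair, and it makes this a correction of a stated figure rather than a threat to the trial.

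Second, falling below 80% depends on a continuity correction that the article never mentions, while the planned analysis is a baseline-adjusted regression giving risk ratios. Without the correction, power stays above 80% in every case above. This stands as a caveat on the power figure. It does not rescue the plan's arithmetic, because the uncorrected formula gives 312 and 170, not 330 and 183. The shortfall in numbers, 320 against 330, needs no formula.

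Third, the manager part is weaker. The difference between 200 and 204 is under 2% and fits rounding to 50 per factory, and the multiplication error is shown only for workers. The 195 is explained under Limitations: one factory had too few managers, so all were recruited. That is an enrolment fact, not a planning error. These points stand; the shortfall of 180 against 183 stands too.

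Fourth, the Limitations section already says that further loss will reduce power. It describes loss beyond what was allowed for, however, and the point here is that the stated allowance was itself not fully provided.

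**Conclusion.** The stated figure is wrong as written. Allowing for 20% loss takes 330 to 413 per arm, not 396, and the 400 recruited tolerate 17.5% loss. At the stated loss the worker sample is 10 per arm below the plan's own requirement. The planned manager sample is 3 per arm below, and the intervention arm as enrolled is about 7 below (175.5 against 183).

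The practical effect is minor: power of 78.8% for workers, and 79.4% (planned) or about 78.9% (as enrolled) for managers. The counts rest only on the article's figures. The power figures assume a relative effect, a two-sided 5% test with continuity correction, and independent participants. The first two are inferred from reproducing 330 and 183. The third matches the stated calculation, which includes no allowance for clustering by factory.

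**What to change.** Correct the text; no further recruitment is asked for. Suggested wording for workers:

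> Recruiting 400 workers per arm retains 320 after 20% loss, giving about 79% power by the continuity-corrected two-proportion formula before any allowance for clustering. Retaining the required 330 per arm needs loss of no more than 17.5%.

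For managers, state that 195 and 200 were enrolled, that 10% loss leaves about 175 and 180, and that keeping 183 needs loss of no more than 6.2% and 8.5% respectively. Name the formula used for both samples.

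Any power calculation that allows for clustering should start from 320 workers per arm (80 per factory). As an option, since workers are already contacted every two months and endline is planned for September to November 2018, the team could aim for worker loss of no more than 17%.

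The cost is a few sentences and slightly less favourable stated figures. The optional retention aim would be an operational choice on top of that.
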